### Eligibility criteria

2.2

#### Inclusion criteria

2.2.1

• Adult men and women aged 19 years or older and 75 years or younger.• Diagnosis of FD according to the Rome IV criteria: o Presence of at least one symptom among postprandial fullness, early satiation, epigastric pain, or epigastric burning. o Symptoms must have developed at least 6 months before screening and persisted for the past 3 months without organic findings.• Dyspepsia severity of 40 points or higher on a 0–100 mm visual analog scale (VAS).• Willingness to refrain from initiating any new treatments related to dyspepsia during the clinical trial period.• Signed written informed consent, approved by the Institutional Review Board (IRB), after receiving a thorough explanation and voluntarily agreeing to participate in the study.

#### Exclusion criteria

2.2.2

Diagnosis of organic diseases such as peptic ulcers, esophageal cancer, MALT lymphoma, gastric cancer, colorectal cancer, or biliopancreatic diseases (asymptomatic gallstones are exempted) within 1 year prior to screening.Symptoms of gastroesophageal reflux disease or irritable bowel syndrome that are more severe than dyspepsia symptoms.Presence of alarm symptoms, including severe weight loss, hematochezia, dysphagia, odynophagia, or persistent vomiting.Significant neurological or psychiatric history or current conditions, including major depressive disorder, anxiety disorder, schizophrenia, anorexia nervosa, or epilepsy.Serious organic diseases (e.g., heart failure, angina, myocardial infarction, arrhythmia, valvular disease, malignant tumors, or stroke).History of gastrointestinal surgery (appendectomy permitted if performed more than 6 months prior to trial participation).Use of medications affecting the gastrointestinal tract, such as proton pump inhibitors, histamine receptor antagonists, antacids, gastrointestinal motility agents, fundus relaxants, mucosal protective agents, anticholinergics, adsorbents, antiflatulents, antiemetics, emetics, gastrin receptor antagonists, prostaglandin analogs, or *Helicobacter pylori* eradication therapy within 2 weeks prior to screening.Receipt of Korean traditional treatments such as acupuncture, herbal medicine, or moxibustion for dyspepsia within 2 weeks prior to screening or plans to receive such treatments during the study period.Use of antibiotics within 3 months prior to screening.Use of probiotic supplements within 1 month prior to screening (participation allowed if probiotics have been taken continuously for more than 1 month prior to screening without planned dosage changes during the trial).Severe liver or kidney dysfunction (as defined by AST or ALT levels more than three times the upper limit of normal, or serum creatinine levels more than twice the upper limit of normal at screening).History of significant alcohol or substance abuse.Pregnant or breastfeeding women, or women of childbearing potential unwilling to use effective contraception during the trial period.Conditions such as galactose intolerance, Lapp lactase deficiency, or glucose–galactose malabsorption.Known hypersensitivity to investigational medicinal products.Use of other investigational medicinal products within 3 months prior to the study.Chronic diseases not well controlled despite appropriate treatment (posing life-threatening risks, requiring hospitalization, causing severe physical disability, or substantially affecting daily life due to conditions such as hypertension or diabetes).Determined unsuitable for trial participation by the investigator or trial director for any other reason.

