Empirically, herbal formulations such as *Yijung-tang* (*Lizhong-tang*, YJT) for spleen deficiency (15, 16), *Pyeongwi-san* (*Pingwei-san*, PWS) for food stagnation (17), and *Shihosogan-tang* (*Chaihu Shugan-tang*, SST) for liver depression (18) are widely used in the treatment of FD. In a preliminary study, these formulations were administered to patients with FD to develop an machine learning-based predictive algorithm for anticipating herbal medicine responses (19). Over an 8-week treatment period, data were collected from various sources, including blood, fecal, and saliva samples, as well as questionnaires and traditional diagnostic devices. This comprehensive dataset was used to construct the machine learning-based prediction system, which was designed to propose typical pattern differentiation types. Building on this foundational work, the present study aims to validate the predictive accuracy of the machine learning-based prediction algorithm. By randomly assigning patients with FD to receive YJT, PWS, or SST based on the machine learning prediction—or one of the remaining herbal medicines not determined by the algorithm—the study seeks to enhance the objectivity and reproducibility of traditional Korean medicine treatments. This approach may provide a pathway toward more personalized and effective patient outcomes.

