#### Study design and allocation

2.1.1

This study is a randomized, assessor-blinded, parallel-group, open-label, multicenter clinical trial. It will be conducted at two Korean medical hospitals: Kyung Hee University Hospital at Gangdong and Dongguk University Ilsan Oriental Medical Hospital. Participants who voluntarily sign the informed consent form will undergo screening examinations during their initial visit (screening visit), including interviews, vital sign measurements, questionnaire surveys, assessments with Korean medicine diagnostic devices, and laboratory tests. Eligible participants will then be enrolled. Within 2 weeks of the screening visit, participants will be randomly assigned to either the ACCORD group, which will receive YJT, PWS, or SST based on a machine learning–driven herbal response prediction algorithm, or the DISCORD group, which will be randomly assigned one of the two herbal medicines not selected by the prediction algorithm from the three options. This ACCORD vs. DISCORD design is specifically employed to validate the algorithm’s discriminative ability—that is, whether the algorithm can accurately distinguish the optimal treatment from suboptimal alternatives for an individual patient. This validation of predictive accuracy is a necessary step before evaluating clinical utility against standard care.

The machine learning algorithm employed in this trial was developed in a prior preliminary clinical study (*N* = 265) (19) (the resulting paper detailing the development methodology is currently under review; Supplementary material 1). The algorithm utilizes the XGBoost (Extreme Gradient Boosting) regressor framework. The objective of the model is a regression task: to predict the magnitude of symptom improvement (effect size) for each of the three herbal formulations (YJT, PWS, and SST). The prediction system recommends the formulation expected to yield the greatest therapeutic benefit for the individual.

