The ground truth (target variable) for model training was the observed change in the Gastrointestinal Symptom (GIS) score from baseline to 8 weeks in the preliminary study. The models were trained using comprehensive baseline data as input features. These features included demographics (e.g., age, sex, and FD duration); patient-reported outcomes and questionnaires (e.g., GIS, and various pattern identification questionnaires); data from Korean medicine diagnostic devices (e.g., tongue diagnosis system, radial pulse analyzer, and digital algometer readings); and laboratory test results (e.g., blood chemistry).

During development, the dataset was split into training (80%) and test (20%) sets for internal validation. Hyperparameter tuning was conducted using RandomizedSearchCV with 5-fold cross-validation on the training data. To mitigate overfitting due to high data dimensionality, an iterative feature selection process was employed to enhance model robustness. The final models demonstrated robust predictive accuracy on the independent test set, confirming their capability to predict treatment responses and discriminate the relative effectiveness among the herbal formulations. Detailed methodology of the algorithm development is provided in Supplementary material 1. The algorithm for prediction system employed in this trial is a locked version (v1.1) that will not be updated during the study period. The prospective validation of this locked algorithm in a new cohort is essential for evaluating its generalizability and mitigating potential biases or overfitting inherent in the preliminary training dataset.

All groups will take the assigned clinical trial medications for 8 weeks. Participants will attend clinic visits at 4-week intervals until week 8 for evaluation of clinical variables, including vital signs, questionnaire surveys, and assessments with Korean medicine diagnostic devices (heart rate variability [HRV], tongue diagnosis, pulse diagnosis, and abdominal diagnosis). In addition, telephone visits will be conducted at 2-week intervals (weeks 2 and 6) to assess whether FD-related pain or discomfort has moderately improved since the previous treatment (Figure 1). Before and after taking the herbal medicine, blood samples (at screening and week 8) and stool and saliva samples (at weeks 0 and 8) will be collected to analyze blood and fecal metabolites as well as gut and oral microbiomes. A detailed assessment schedule is provided in Table 1.

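### The eligibility criteria do not bar preliminary-study participants, so the validation sample is not guaranteed to be independent of the data that built the algorithm

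*Protocol article*

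**What the plan says.** Section 2.1.1 of the protocol article gives the algorithm's origin: "developed in a prior preliminary clinical study (*N* = 265" participants). The Introduction says of the three formulas that "these formulations were administered to patients with FD to develop an machine learning-based predictive algorithm". The training target "was the observed change in the Gastrointestinal Symptom (GIS) score from baseline to 8 weeks in the preliminary study", which is the instrument and time point of this trial's primary endpoint (2.8.2). For development, "the dataset was split into training (80%) and test (20%) sets for internal validation".

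The same section states why the present trial is needed: "The prospective validation of this locked algorithm in a new cohort is essential for evaluating its generalizability and mitigating potential biases or overfitting".

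Sections 2.2.1 and 2.2.2 then print a detailed list of criteria. None mentions the preliminary study. Three exclusions come near:

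- "Use of other investigational medicinal products within 3 months prior to the study";
- Korean traditional treatment for dyspepsia, including herbal medicine, in the 2 weeks before screening or planned during the study;
- a closing item that leaves other grounds of unsuitability to the investigator or trial director.

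Recruitment (2.3) is by open advertising, including notices inside the participating institutions and outreach to communities of people with functional dyspepsia. No check for earlier participation is described.

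**The concern.** A validation study answers its question cleanly only if its patients did not help to build the model. Here the purpose is stated as validation in new patients, but the rules that screeners apply do not enforce it.

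For a returning patient from the training split, the model was fitted to that person's own 8-week GIS change on one of the three formulas. If the recommendation at re-enrolment still reflects that fit, ACCORD would tend to receive a formula on which the patient had already done well. That advantage says nothing about skill in new patients. It is the overfitting that the trial is meant to test for.

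At stake is the independence of the sample and, to a lesser degree, the size of the contrast. Undisclosed overlap would also leave readers unable to judge either.

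**Working it through.** **1. Would a former participant be eligible?** Take someone who completed the preliminary study more than 3 months ago, has had no traditional treatment for dyspepsia in the last 2 weeks, still meets Rome IV and scores at least 40 on the VAS. The investigational-product window has passed, the washout is met, and the discretion item does not name prior participation. Nothing else in 2.2.1 or 2.2.2 excludes this person on account of the earlier study.

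**2. Who are the 265?** With the stated split, 0.80 × 265 = 212 were used for training and 0.20 × 265 = 53 for internal testing. The 53 were not used for fitting under that split, but they belong to the development dataset and are not a new cohort either.

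**3. The plan's own sample size.** Inputs from 2.7 and 2.8: 2.72 (read here as the between-group difference), SD 4.57, two-sided 5%, 1:1 allocation, 10% dropout. Power is not stated; 80% is assumed.

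n per group = 2 × (1.960 + 0.842)² × 4.57² / 2.72² = 44.3, rounded up to 45. Then 45 / 0.90 = 50 per group, 100 in total. The stated figure is reproduced. Excluding former participants alters none of these inputs.

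**4. Standard error of the contrast.** SE = 4.57 × √(2/45) = 0.96 GIS points.

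**5. Illustrative bias.** Neither the overlap nor the in-sample effect is given, so every input here except the SD is an assumption. Suppose the algorithm has no skill in new patients. Let person-by-formula response make up a share r of the outcome variance. Let the prediction for the formula taken earlier equal a weight s times the patient's earlier observed response. Let the other two predictions be noise with SD 0.5 × 4.57, and recommend the largest of the three. Simulating 400,000 patients gives the spurious advantage per re-enrolled training patient:

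| r | s | GIS points |
|---|---|---|
| 0.25 | 0.5 | 0.48 |
| 0.25 | 0.8 | 0.58 |
| 0.50 | 0.5 | 0.97 |
| 0.50 | 0.8 | 1.16 |

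Overall shift = overlap × per-patient advantage. Lowest: 0.10 × 0.48 = 0.05. Highest: 0.20 × 1.16 = 0.23. Relative to the SE, that is 0.05/0.96 = 0.05 to 0.23/0.96 = 0.24. With no true effect, the two-sided rejection rate moves from 5.0% to between 5.03% and about 5.7%.

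**6. Sensitivity to the assumptions.**

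- Weaker: r of 0.05-0.10 with s of 0.5-0.8 gives 0.09-0.23 points per re-enrolled patient, so about 0.01-0.05 overall at 10-20% overlap. With r = 0.25 and s of 0.1-0.2, the per-patient figure is 0.13-0.25.
- Harsher: suppose returning patients show the full planning difference of 2.72 and new patients show none. Overlap of 5%, 10%, 20% and 30% then gives an expected contrast of 0.14, 0.27, 0.54 and 0.82, and a rejection rate of 5.2%, 5.9%, 8.7% and 13.5%. Nothing in the article supports an in-sample difference or an overlap of that size.

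**The case against.** The strongest case against is that the consequence is small and uncertain. Most of this stands.

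- The article gives no sites, dates or consent terms for the preliminary study, so overlap may be zero.
- The model's inputs (questionnaires, device readings, laboratory tests) are measured again at screening. A returning patient enters with new values, and nothing suggests that the old record is looked up. The model may recall little of that person's response.
- Development used cross-validation and feature selection to limit overfitting.
- A returning patient must again score at least 40 on the VAS, so lasting responders are the least likely to return. Upward bias is the likely direction but is not assured.

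A reader might go further and infer that the trial cannot test generalizability, or that all 265 outcomes trained the model. The article supports neither. No overlap is documented, the illustrative shift is at most about a quarter of a standard error, and about 53 of the 265 were held out from fitting. Familiarity with a formula from open-label use is not specific to former participants either, since these are approved, insurance-covered products.

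Two further objections do not succeed. One is that a condensed article may omit a criterion found in the full protocol. But the printed list goes down to lactase deficiency and the timing of an appendectomy, and prior participation is an eligibility rule, not an analysis detail. If the full protocol contains it, the sponsor need only cite it. The other is that describing the cohort as new, together with investigator discretion, is enough. A description of intent does not bind screeners, and a discretionary item is not a rule.

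**Conclusion.** The point holds as a gap between the stated purpose and the printed eligibility rules. Participants of the preliminary study can enrol once the 3-month and 2-week windows have passed. If any do, the sample is not fully independent of the development data and the contrast could be slightly inflated.

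The size cannot be computed from the article. The range of 0.05-0.23 GIS points rests on assumed overlap of 10-20%, an assumed 25-50% share of person-by-formula variance and an assumed fit weight of 0.5-0.8. It is 2-8% of the 2.72 planning value. Confidence is high that the criterion is absent from the printed list, and low that material bias would follow. This is a worthwhile, inexpensive improvement and not a threat to the trial's validity.

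**What to change.** Add one exclusion to 2.2.2: participation at any time in the preliminary clinical study whose data were used to develop the prediction algorithm. It should cover training and test participants alike. Verify it at screening against that study's enrolment list.

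If any such participants are already enrolled, report how many and in which group, and repeat the primary analysis without them as a sensitivity analysis.

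The cost is one eligibility line, submitted as an amendment to both review boards and updated on the registries (2.11), plus a look-up at screening. The sample size stays at 45 evaluable per group and 100 in total. The downside is the loss of a few otherwise eligible patients.

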
### Participant recruitment

2.3

Participants will be recruited through regular promotional activities in mass media channels, including newspaper inserts and daily newspapers. Promotional materials will also be posted on bulletin boards and websites both within and outside the participating institutions. Regional advertisements such as subway and bus ads, as well as apartment bulletin board postings, will be used. Online platforms, including websites and applications, will additionally be utilized for advertising. Cooperation will further be sought from online communities, local gatherings, and clubs frequented by individuals with FD to generate interest and encourage participation.

### Interventions

2.4

#### Information and management of investigational medicinal products

2.4.1

The herbal medicine formulations used in this study are YJT, PWS, and SST, all of which are brown powders manufactured by HanKook ShinYak Co., Ltd. and Kyungbang ShinYak Co., Ltd. These products are approved for use under Korean medicine health insurance and are classified as gastrointestinal drugs by the Ministry of Food and Drug Safety (MFDS). They are administered orally at a recommended dosage of one packet three times daily between meals and should be stored in airtight containers at room temperature (1–30 °C). Each product has a shelf life of 36 months from the manufacturing date. The detailed composition of each herbal product is summarized in Table 2. These formulations are intended to support gastrointestinal health and are covered by Korean health insurance. Their production adheres to MFDS standards, ensuring quality and efficacy.

**Table 2 tab2:** Components of *Yijung-tang* (YJT), *Pyeongwi-san* (PWS), and *Shihosogan-tang* (SST).

Product	Composition (per packet)	Manufacturer
YJT	*Panax ginseng* 2.5 g, *Atractylodes macrocephala* 2.5 g, *dried Zingiber officinale* 2.5 g, *Glycyrrhiza uralensis* 1.25 g	HanKook ShinYak Co., Ltd.
PWS	*Atractylodes macrocephala* 2.5 g, *Citrus unshiu* 1.75 g, *Magnolia officinalis* 1.25 g, *Glycyrrhiza uralensis* 0.75 g, *Zingiber officinale* 0.5 g, *Ziziphus jujuba* 0.67 g	HanKook ShinYak Co., Ltd.
SST	*Bupleurum falcatum* 1.5 g, *Citrus unshiu* 1.5 g, *Cnidium officinale* 1.25 g, *Paeonia lactiflora* 1.25 g, *Poncirus trifoliata* 1.25 g, *Cyperus rotundus* 1.25 g, *Glycyrrhiza uralensis* 0.63 g	Kyungbang ShinYak Co., Ltd.

#### Criteria for discontinuing or modifying allocated intervention/comparator

2.4.2

Discontinuation or modification of the allocated herbal medicine may occur under the following conditions:Development of clinically significant adverse events, including allergic reactions to herbal components or worsening gastrointestinal symptoms judged to be related to the study medication.Participant request to stop or change the assigned intervention at any time, without prejudice to subsequent medical care.Marked deterioration of functional dyspepsia symptoms requiring additional treatment outside the trial protocol.Investigator decision based on medical judgment, protocol non-compliance, or new contraindications (e.g., pregnancy).

Participants discontinuing the allocated intervention will, wherever possible, be encouraged to remain in the trial for outcome assessments to minimize attrition bias.

#### Concomitant medications and treatments

2.4.3

##### Permitted concomitant medications and treatments

2.4.3.1

Concomitant medications judged by the principal investigator or sub-investigator to be unlikely to affect the interpretation of study results may be allowed. These may include medications for unrelated conditions or treatments for adverse events that arise during the trial. Whenever possible, the type and dosage of such medications should remain unchanged throughout the study period. All concomitant medications and treatments must be documented in the case report form (CRF), including product name, indication, total daily dose, route of administration, and duration of use. If the dosage of a pre-existing medication is modified or if additional medications are initiated during the trial, this must be promptly reported to the investigator and recorded in the CRF.

##### Prohibited concomitant medications and treatments

2.4.3.2

The use of new medications or treatments specifically for dyspeptic symptoms is prohibited during the study. If such use occurs, the principal investigator will determine whether the participant should be withdrawn from the trial or excluded from the statistical analysis. The use of antibiotics is strictly prohibited during the study period. Probiotic preparations may be permitted if participants have been taking them continuously for at least 1 month before screening and if the dosage and regimen remain unchanged during the trial. Any change in dosage or regimen during the trial will be considered a protocol violation, and the participant will be withdrawn from the study.

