Randomization tables will be generated using SAS® Version 9.4 (SAS Institute Inc., Cary, NC, United States) by a medical statistician independent of the trial interventions and assessments. The randomization list will allow for the registration of 50 participants per institution. The randomization system will be managed by a medical statistician, independent of the trial, serving as the system administrator. Investigators will be able to access participant identification codes and group allocation information only with administrator approval. To ensure allocation concealment, a centralized, web-based randomization system will be utilized. This system will be managed by the independent medical statistician serving as the administrator. Once a participant is confirmed eligible and enrolled, the investigator will access the web-based system, which will then reveal the participant’s unique identification code and group allocation. The system ensures that the allocation sequence remains concealed until the point of assignment. Evaluation of participant outcomes will be conducted by staff who will not prescribe medications or access medical records and case report forms. Evaluators will ask only the questions necessary for assessment and will remain blinded to participant group assignments. These procedures, including centralized randomization managed by an independent statistician, allocation concealment, and assessor blinding, are implemented to minimize potential selection and assessment bias throughout the trial.

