#### Statistical analysis and evaluation of efficacy endpoints

2.8.2

The primary efficacy endpoint is the between-group difference in the GIS score at week 8 (ACCORD vs. DISCORD). The primary endpoint will be analyzed using the MMRM, with treatment group and visit time as fixed factors and participant as a random factor.

The secondary efficacy endpoints include TDS, AR for dyspepsia, OTE, dyspepsia VAS, FD-QoL, Spleen Qi Deficiency Questionnaire, Stomach Qi Deficiency Questionnaire, Food Retention Questionnaire, Cold–Heat Pattern Questionnaire, and Deficiency–Excess Pattern Questionnaire. Categorical secondary variables will be analyzed using the chi-square test or Fisher’s exact test.

To address the issue of multiple comparisons for the multiple secondary efficacy endpoints, the Benjamini-Hochberg procedure (False Discovery Rate, FDR) will be applied to adjust the *p*-values. The primary endpoint will be tested at a significance level of 0.05 without adjustment. Exploratory outcomes will not be adjusted for multiplicity, and their results will be interpreted as hypothesis-generating.

Exploratory subgroup analyses (by assigned herbal formula and by DISCORD subgroup) will be performed to assess the consistency of treatment effects; these analyses are hypothesis-generating and are not powered for confirmatory inference. Effect modification will be explored using treatment-by-subgroup interaction terms within the mixed model, and results will be reported as effect estimates with 95% confidence intervals and interpreted cautiously.

For the primary outcome, missing data will be handled using the last observation carried forward (LOCF) method. In addition, multiple imputation will be applied as a sensitivity analysis to assess the robustness of results under different assumptions regarding missingness. The main analyses will be conducted on an intention-to-treat basis, with per-protocol analyses performed for comparison.

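### The prohibited-treatment rule lets the principal investigator exclude randomised participants from an unspecified analysis, which as written conflicts with the intention-to-treat main analysis

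*Protocol article*

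**What the plan says.** **Prohibited treatment (section 2.4.3.2).** The rule opens: "The use of new medications or treatments specifically for dyspeptic symptoms is prohibited during the study". If it is broken, "the principal investigator will determine whether the participant should be withdrawn from the trial or excluded from the statistical analysis". No analysis set, criterion or timing is given. A separate rule in the same section covers probiotics: a change of dose or regimen "will be considered a protocol violation, and the participant will be withdrawn from the study".

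**Analysis population (section 2.8.2).** "The main analyses will be conducted on an intention-to-treat basis, with per-protocol analyses performed for comparison". Missing primary data are filled by last observation carried forward, with multiple imputation as a sensitivity analysis.

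**Adherence (section 2.4.4).** Participants below 70% adherence may be left out, but here the text names the per-protocol analysis.

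**Stopping the intervention (section 2.4.2).** One listed reason is deterioration that calls for treatment outside the protocol. Participants who stop will, where possible, "be encouraged to remain in the trial for outcome assessments to minimize attrition bias".

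**Blinding (sections 2.1.1 and 2.1.2).** "This study is a randomized, assessor-blinded, parallel-group, open-label, multicenter clinical trial". On outcome assessment: "Evaluators will ask only the questions necessary for assessment and will remain blinded to participant group assignments". On investigators: "Investigators will be able to access participant identification codes and group allocation information only with administrator approval". The same section has the web system show the allocation to the investigator once an eligible participant is enrolled.

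**The concern.** An intention-to-treat analysis keeps everyone who was randomised. A rule that lets one person remove participants from the statistical analysis, without saying which analysis, leaves the primary population undetermined at the point where it matters most.

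The trigger makes this more than a drafting slip. Starting another dyspepsia treatment happens after randomisation and is plausibly a sign that the assigned formula is not working, which is what the GIS score measures. If the algorithm discriminates as hoped, the event should be commoner in DISCORD. Removing those participants then selects on something related to both arm and outcome.

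Discretion adds a second route to bias. With no criterion, similar cases may be handled differently, and in an open-label trial the person deciding probably knows the arm. With 50 participants per group, a few such decisions can move the result.

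**Working it through.** **1. The rules side by side**

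| Section | Trigger | Consequence | Analysis named |
|---|---|---|---|
| 2.4.3.2 | New dyspepsia treatment | Withdrawal or exclusion, decided by the principal investigator | None; refers only to the statistical analysis |
| 2.4.4 | Adherence below 70% | Possible exclusion | Per-protocol |
| 2.4.2 | Stopping the intervention, including for outside treatment | Encouraged to stay for outcomes | Not applicable |
| 2.8.2 | None | Main analyses | Intention-to-treat |

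Where the authors meant per-protocol, in 2.4.4, they said so. Section 2.4.3.2 has no such limit, so its literal reach includes the main analysis. Sections 2.4.2 and 2.4.3.2 can also apply to the same event and point different ways.

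**2. The plan's own figure**

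Inputs from section 2.7: 2.72, SD 4.57, 45 per group, 10% dropout, 100 in total. Two-sided alpha of 0.05 is from section 2.8. Power is not stated; 80% is assumed. The text attaches 2.72 to both groups, and it is read here as the between-group difference because that reading reproduces the sample size.

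n = 2 × (1.960 + 0.842)² × (4.57 / 2.72)² = 44.3, so 45 per group. Then 45 / 0.90 = 50 per group, 100 in total. This agrees with the plan. At 85% or 90% power the result would be 51 or 60 per group.

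**3. Bias from removing users of other treatment**

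Let q be the share removed in an arm, and g the amount by which their improvement falls short of the others in that arm. The retained mean exceeds the full-arm mean by q × g, so:

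retained difference = 2.72 − (q_DISCORD − q_ACCORD) × g

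All rates and gaps below are assumptions; the documents give none.

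- 10% vs 2%, g = 5: 2.72 − 0.08 × 5 = 2.32 (−15%)
- 10% vs 2%, g = 8: 2.72 − 0.08 × 8 = 2.08 (−24%)
- 15% vs 5%, g = 5: 2.72 − 0.10 × 5 = 2.22 (−18%)

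If the other treatment worked well enough to make g negative, the same formula would give a difference above 2.72.

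**4. Selective and even-handed exclusion, by simulation**

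Normal outcomes, SD 4.57, 50 per arm, two-sample t-test. The numbers of exclusions are assumed.

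No true effect, worst responders dropped from ACCORD only:

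| Dropped | Type I error | Spurious difference (GIS points) |
|---|---|---|
| 0 | 0.05 | 0.0 |
| 1 | 0.06 | 0.2 |
| 2 | 0.08 | 0.4 |
| 3 | 0.11 | 0.55 |
| 5 | 0.18 | 0.86 |

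True difference 2.72, same rule in both arms, applied to participants more than 4 points below the DISCORD mean:

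| Share of these excluded | Estimate | Power |
|---|---|---|
| None | 2.72 | 0.84 |
| Half | 2.36 | 0.75 |
| All | 1.86 | 0.61 |

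So even consistent use of an outcome-related exclusion shrinks a real effect, and one-sided use can create a false one.

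**The case against.** The best defence is that the sentence was meant for the per-protocol set. Section 2.8.2 fixes the main analysis as intention-to-treat, prohibited medication is a usual per-protocol exclusion, and analysis sets are commonly defined in an SAP, which is not shown. That may well be the intention. It does not remove the problem: this is a rule the protocol states, not a detail it leaves out, and an SAP that defines intention-to-treat would still contradict section 2.4.3.2 as worded.

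Other parts of the defence stand and limit the point:

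- A reader might infer that an unblinded principal investigator will exclude participants after seeing their results. The documents do not say this. Unblinding follows from the open-label design and the display of allocation at assignment, while section 2.1.2 also makes access subject to administrator approval. Nothing says that outcome data are seen when the decision is made, and separate blinded evaluators collect outcomes.
- A reader might count withdrawal as a further breach of intention-to-treat. It is not: a withdrawn participant can stay in that set, with missing values handled under section 2.8.2. It does cost data. GIS is scheduled at screening, week 4 and week 8 (Table 1), so withdrawal before week 4 leaves only the screening value to carry forward.
- Nothing links a probiotic change to poor response or to arm, so the selection argument does not extend to that rule.
- Section 2.4.2 states a qualified aim, so its relation to 2.4.3.2 is a tension to reconcile, not a flat contradiction.
- The magnitudes rest on assumptions. Gaps of 5 and 8 points exceed one SD (8 / 4.57 is about 1.75), and an effective outside treatment could shrink or reverse them.

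**Conclusion.** The point holds in a limited form. As worded, section 2.4.3.2 allows case-by-case exclusion of randomised participants from an unspecified analysis, after an event plausibly related to poor response, and this conflicts with the intention-to-treat main analysis. It permits biased exclusion; it does not plan it.

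The size cannot be known from the documents, because they do not say how often the rule would be used or how those participants would fare. Under the assumed rates and gaps in step 3, a difference of 2.72 falls to between 2.08 and 2.32, towards the null. One-sided use works the other way: three selective exclusions from ACCORD would roughly double the type I error. The direction is therefore open. The conflict bears on who enters the primary analysis and is cheap to remove, so it should be corrected before any such decision is taken.

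**What to change.** 1. Reword the exclusion clause in section 2.4.3.2 along these lines: use of a prohibited dyspepsia treatment is recorded and affects membership of the per-protocol set only, decided by criteria fixed in advance and applied by staff blind to allocation before database lock.
2. State in section 2.8.2 that all randomised participants stay in the intention-to-treat analysis with all data collected.
3. Reconcile the withdrawal wording in section 2.4.3.2, for both new dyspepsia treatment and probiotic change, with the aim in section 2.4.2 of keeping participants for outcome assessment. Which clinical rule should apply is for the investigators, and no position is taken on it here.

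The sample size stays at 50 per group and no visits are added, since weeks 4 and 8 are already scheduled. If all 50 per group are analysed, power at the planning values is about 0.85, against 0.81 with 45. The cost is a short amendment, approval by both IRBs before it takes effect, and updates to both registry entries, as section 2.11 requires.
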